### Secondary outcome measures

Secondary outcomes will be specific anxiety symptoms (STAI-Y), coping skills (CISS questionnaire), depression (EPDS questionnaire) in relation to neurodevelopmental and behavioural scores.

The STAI-Y^31^ is a 40-item self-report questionnaire assessing trait anxiety (20 items) and state anxiety (20 items). Each item is rated on a four-point Likert scale, from 1 (= almost never) to 4 (= almost always), with higher scores indicating greater anxiety.The CISS^32^ is a 48-item self-report questionnaire assessing individual coping styles in response to stress. It evaluates three primary coping dimensions: task-oriented coping, emotion-oriented coping and avoidance-oriented coping. Each item is rated on a five-point Likert scale, from 1 (= not at all) to 5 (= very much), with higher scores indicating greater use of the coping style.The PCL-5^35 36^ is a 20-item self-report questionnaire assessing symptoms of PTSD as defined by the DSM-5. Symptom severity is evaluated across four clusters, namely: intrusion, avoidance, negative alterations in cognition and mood and arousal and reactivity. Each symptom is rated on a five-point Likert scale, from 0 (= not at all) to 4 (= extremely), depending on its severity in the last month. A score above the cut-point score of 31–33 indicates PTSD.The EPDS^33 34^ is a 10-item self-report questionnaire assessing postpartum depression symptoms. Each item is rated 0 to 3 depending on the frequency of symptoms in the last week. Total scores range from 0 to 30, with scores above the cut-off point of 12.5 indicating postpartum depression.The ASQ-3^37^ is a parental questionnaire for children aged 1 month to 5 years 6 months that screens five developmental domains: communication, gross motor, fine motor, problem-solving skills and adaptive skills. Each domain contains six items, rated 10 (=yes), 5 (=sometimes) or 0 (= not yet) by the parent or caregiver depending on their child’s current skills. The ASQ-3 is a recommended screening tool of child development with good psychometric properties.^37 41^

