**Figure 1 F1:**
[figure not shown]
Study visit and data collection schedule. CHD, congenital heart disease; GA, gestational age.

At Time 2 (after surgery, before the child is discharged from hospital), a post-partum depression questionnaire (EPDS), an anxiety questionnaire (STAI-Y) and a coping scale (CISS) will be administered to the participants, at the most convenient time for them. Finally, an information note concerning the child’s next visit will be given to the parents along with parental consent for the child’s participation.

At Time 3, a follow-up consultation will be conducted with mothers and their 12 to 18 months old child. The mother will be offered a psychological state questionnaire (SCL-90-R), an anxiety scale (STAI-Y), a coping scale (CISS) and a post-traumatic stress scale (PCL-5). A neurodevelopmental examination using the standardised ASQ-3 and Bayley-4 tests will be conducted, including an assessment of the child’s behavioural and socio-emotional development, and their neurodevelopment (cognition, language, fine and gross motor skills, as well as psychosocial development). No measures will be collected for the co-parent at Time 3. Figure 2 summarises the measurements.

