#### Secondary objectives

##### Aims 2 and 3

In order to study changes over time (ie, evolution of maternal mental health) in the scores obtained on the self-report questionnaires (SCL-90-R, STAI-Y, CISS, PCL-5, EPDS) completed by the mother and to study changes as a function of medical, sociodemographic and lifestyle factors, a linear mixed model will be applied. This model takes into account the random effect induced by the analysis of three repeated measurements. The cofactors tested (fixed effects) will be the variables likely to influence the scores on these self-report questionnaires (medical, sociodemographic and lifestyle). The results of the linear mixed model are expressed for each factor in the form of a coefficient corresponding to the variation brought about by this factor on the basal score (intercept). A positive coefficient indicates a score-raising effect, while a negative coefficient indicates a score-lowering effect. For the time effect, the coefficient reflects the variation during the follow-up, while for the other factors, the estimate reflects the variation induced by the presence of the factor. The interactions between the co-factors and time will also be tested. A similar methodology will be applied for each score.

##### Aim 4

We will use a structural equation model to estimate simultaneously the relationships among maternal mental health (as captured by SCL-90-R, STAI-Y, CISS, PCL-5 and EPDS scores), prenatal factors (medical, sociodemographic and psychological) and child development (Bayley-4 and ASQ-3).

The structural pathways linking these three latent constructs, whereby maternal mental health impacts prenatal factors, which in turn influence the child’s development, while also allowing for a residual direct effect of maternal mental health on developmental outcomes.

We will quantify the mediating role of each block of prenatal factors by estimating the proportion of the effect of maternal mental health on child development that is transmitted through those factors. The model will be fitted using robust maximum likelihood estimation, with bootstrapping to derive CIs for indirect effects.

##### Aim 5

The GSI of the SCL-90-R will be used as an indicator of co-parent mental health. It is a standardised score with a T-score (mean 50, SD 10). The Bayley-4 cognitive score will be used as an indicator of neurodevelopment in children with CHD at age 1. This is an exploratory analysis, independent of the primary outcome.

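### Aim 4 pools the parent-rated ASQ-3 with the Bayley-4 as one outcome, against a purely mother-reported exposure, so shared-rater variance can enter the direct effect and the mediated share

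*Protocol article*

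**What the plan says.** In the Data analysis plan (Secondary objectives, Aim 4), the exposure is "maternal mental health (as captured by SCL-90-R, STAI-Y, CISS, PCL-5 and EPDS scores" and the outcome is "child development (Bayley-4 and ASQ-3". The text then refers to "The structural pathways linking these three latent constructs", so the two developmental tools serve one outcome construct. Estimation is by robust maximum likelihood, with bootstrap intervals for the indirect effects, and the share of the effect passing through each block of prenatal factors is to be reported.

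On who rates what:
- **Exposure.** The paragraph on Aims 2 and 3 describes the same five scales as "SCL-90-R, STAI-Y, CISS, PCL-5, EPDS) completed by the mother".
- **ASQ-3.** Secondary outcome measures calls it a parental questionnaire, with items "rated 10 (=yes), 5 (=sometimes) or 0 (= not yet) by the parent or caregiver".
- **Time 3.** Under Procedures, "a follow-up consultation will be conducted with mothers and their 12 to 18 months old child", and no co-parent measures are taken. The PCL-5 appears in the Procedures text at this visit only, which is also when the ASQ-3 is obtained. The same paragraph groups the ASQ-3 with the Bayley-4 as standardised tests and does not mention that a parent supplies the ASQ-3 ratings.

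Aim 1 takes the Bayley-4 cognitive score as its primary indicator of neurodevelopment, and Aim 5 uses the same score.

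**The concern.** When one person reports both the exposure and part of the outcome, the two can correlate through her reporting style or current mood as well as through the child's true development. A single outcome factor cannot tell these sources apart. Covariance between maternal distress and the ASQ-3 is read as an effect on development, diluted by the Bayley-4 indicators but not removed by them. Robust maximum likelihood deals with non-normality and bootstrapping with sampling error; neither deals with a rater effect.

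What is at stake is the quantity that Aim 4 exists to estimate. The mediated share is the indirect effect divided by the indirect plus the direct effect. Rater bias that acts straight from distress to the ASQ-3 loads mainly on the direct path, so it inflates the total effect and shrinks the share. Where a mediator is itself a maternal self-report, such as coping style, bias can also reach the indirect path. The Discussion links the study's findings to preventive strategies, so a reader may act on these estimates.

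**Working it through.** The article gives no figure for Aim 4, so there is nothing of the plan's own to reproduce. The check has two parts.

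**1. Who is likely to rate, and when**

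| Element | Rater in the text | When collected (Procedures text) |
|---|---|---|
| SCL-90-R, STAI-Y, CISS | mother | Time 1; also Time 3 (STAI-Y and CISS at Time 2 too) |
| EPDS | mother | Time 2 |
| PCL-5 | mother | Time 3 only |
| ASQ-3 | parent or caregiver | Time 3 |
| Bayley-4 | not parent-rated in the text | Time 3 |

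With mothers attending Time 3 and no co-parent data collected, the mother is the expected ASQ-3 respondent. That is an inference. Overlap of visit is certain for the PCL-5 only.

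**2. How large the distortion could be (illustration)**

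Every input here is an assumption, because the documents give none of them. Let D be true development, M standardised maternal distress and g the reporting bias:
- Bayley-4 indicator = 0.75 × D + error
- ASQ-3 indicator = 0.60 × D − g × M + 0.3 × (ASQ-3 method factor) + error

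A one-factor model with M as predictor was fitted by maximum likelihood to the implied population covariances. Estimated standardised path from M:

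| Indicators (Bayley-4 + ASQ-3) | True path | g = 0 | g = 0.1 | g = 0.2 | g = 0.3 |
|---|---|---|---|---|---|
| 5 + 5 | 0 | 0.00 | -0.058 | -0.117 | -0.182 |
| 3 + 5 | 0 | 0.00 | -0.083 | -0.171 | -0.270 |
| 1 + 1 | 0 | 0.00 | -0.100 | -0.196 | -0.287 |
| 5 + 5 | -0.20 | -0.198 | -0.254 | -0.313 | -0.377 |

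A hand check uses a plain sum of ten indicators that all load 0.7, with no true effect. The covariance with M is −5g. The variance is about 10 + 90 × 0.49 = 54.1, so the SD is 7.36 (the small g² terms are ignored). The correlation is −5g/7.36, which gives -0.07, -0.14 and -0.20 for g = 0.1, 0.2 and 0.3. This agrees in direction and order of size with the 5 + 5 row.

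For the mediated share, suppose the indirect effect is estimated without distortion and the true total is -0.20. The reported share is then the true share times 0.198/0.254 = 0.78, 0.198/0.313 = 0.63, or 0.198/0.377 = 0.53. In this set-up, the share falls by roughly a fifth to a half.

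A Bayley-only outcome shows no distortion here, but only because the bias was placed on the ASQ-3 alone.

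**The case against.** The best reply has four parts.

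**Detail left to the SAP.** The article outlines the model and need not list indicators, method factors, residual covariances or sensitivity analyses. This stands: their absence is no finding. What is written down is that both tools belong to one outcome construct, and the point concerns that choice.

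**The rater and the occasion.** A reader might infer that the mother certainly completes the ASQ-3 and that exposure and outcome are collected together. The documents do not support either. The ASQ-3 rater is "or 0 (= not yet) by the parent or caregiver". Aim 4 is framed around prenatal mental health: SCL-90-R, STAI-Y and CISS are available from Time 1 and EPDS from Time 2. At Time 3, "The mother will be offered a psychological state questionnaire (SCL-90-R", but nothing says that the Time 3 score enters Aim 4. A stable reporting tendency could still link earlier self-reports to later ASQ-3 ratings.

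**The size.** It would be tempting to quote inflated false-positive rates for Aim 4. At n = 70, a simple correlation test on a pooled score gives about 10%, 22% and 42% for assumed biases of 0.1, 0.2 and 0.3. Those are not error rates of the planned model, which is a structural equation model with indirect effects, and the documents do not show that any such bias exists.

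**Scope and convention.** Aim 4 is secondary and exploratory, several instruments for one construct is a usual design, and Aim 1 already supplies a Bayley-only association. All true. What remains missing is a Bayley-only direct effect, indirect effect and mediated share.

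**Conclusion.** The point holds in conditional form. The article fixes an outcome construct that mixes a parent rating with the Bayley-4, and an exposure construct made only of maternal self-reports. If the mother usually completes the ASQ-3, and if distress colours her answers, the Aim 4 direct effect and mediated share would partly reflect reporting. Both conditions are plausible; neither is stated. With no true effect and five plus five indicators, an assumed bias of 0.1 to 0.3 gives a spurious path of roughly -0.06 to -0.2; fewer Bayley-4 indicators make it larger. Loadings, indicator counts and bias are all assumed, so these figures show the mechanism and do not forecast its size. The primary analysis and Aim 5 are not touched.

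**What to change.** In Aim 4, make the Bayley-4 the child-development outcome, with the cognitive score first as in Aims 1 and 5. Analyse the ASQ-3 in a separate model labelled parent-reported. If the pooled construct is kept, report the Bayley-only direct effect, indirect effects and mediated share beside it, and state in advance that the conclusion rests on those. In either case, record who completes each ASQ-3.

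The cost is a change of analysis wording and one data field, with no added visit or test. The drawback is fewer outcome indicators and some loss of precision. Modelling the rater effect directly is possible but not cheap. Residual covariances between five ASQ-3 domains and five maternal scales would add up to 5 × 5 = 25 parameters, with about 70 evaluable dyads (87 × 0.8 = 69.6), and a method factor is also demanding at that size. The Bayley-only route is therefore the more practical one.

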#### Secondary objectives

*Aim 2*: To describe the evolution of maternal mental health (ie, anxiety, depression and psychological adjustment scores), from the antenatal period to the neonatal postoperative period (after cardiac surgery), and finally when the child with CHD turns 1 year. We predict that maternal psychological distress will decrease over time, as we expect that the most acute period of stress will be closest to the initial diagnosis of fetal CHD (T1, T2 and T3).

*Aim 3*: To identify the medical and sociodemographic factors associated with prenatal maternal psychological distress of women carrying a fetus diagnosed with cyanotic CHD. We hypothesise that lower maternal educational attainment and poor family support as well as fetal factors such as diagnosis of severe CHD (ie, univentricular heart) will be associated with worse prenatal maternal mental health outcomes (ie, overall mental health, anxiety and depression symptoms). The evaluation of scores obtained on self-report questionnaires (SCL-90-R,^29^ State-Trait Anxiety Inventory (STAI-Y),^31^ Coping Inventory for Stressful Situations (CISS),^32^ Edinburgh Postnatal Depression Scale (EPDS),^33 34^ Posttraumatic Stress Disorder Checklist for DSM-5 (PCL-5)^35 36^) completed by the mother will be analysed in relation to medical, sociodemographic and lifestyle factors.

*Aim 4*: To explore the mediating role of prenatal risk factors (ie, medical factors and maternal coping strategies, such as task-oriented, avoidant and emotional coping) in the association of prenatal maternal mental health (ie, distress, anxiety and depression) and neurodevelopment in children with CHD. We will also explore the potential interaction effects between sociodemographic factors and mental health on neurodevelopment in CHD. We hypothesise that expecting mothers with low socioeconomic levels of support and/or with maladaptive coping strategies (eg, avoidant, emotional reactivity) will experience the greatest effects of prenatal distress on their children’s neurodevelopmental outcomes at 1 year of age. The mediating role of medical and psychological antenatal factors (information extracted from the medical record, the interview and the information questionnaire) on the relationship between maternal mental health scores (SCL-90-R, STAI-Y, CISS, EDPS, PCL-5) and the child’s neurodevelopment (Bayley-4,^30^ Ages and Stages Questionnaire-Third Edition (ASQ-3)^37^) will be characterised.

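### Aim 4 describes a structural equation model with one prenatal-factors mediator, then promises the mediating role of each block, which that model cannot give

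*Protocol article*

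**What the plan says.** All of the analysis text below is from the Aim 4 part of the Data analysis plan (Secondary objectives) in the protocol article.

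- One model is fitted: "We will use a structural equation model to estimate simultaneously the relationships among maternal mental health", prenatal factors and child development.
- The second and third constructs are described as "prenatal factors (medical, sociodemographic and psychological) and child development (Bayley-4 and ASQ-3").
- The structure is then given: "The structural pathways linking these three latent constructs, whereby maternal mental health impacts prenatal factors", which act on the child's development, "while also allowing for a residual direct effect of maternal mental health on developmental outcomes".
- The estimand follows: "We will quantify the mediating role of each block of prenatal factors by estimating the proportion of the effect" of maternal mental health that passes through them.
- Inference is by robust maximum likelihood, "with bootstrapping to derive CIs for indirect effects".

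The objective for Aim 4, under Aims and hypotheses, is framed differently. It reads "To explore the mediating role of prenatal risk factors (ie, medical factors and maternal coping strategies", and it gives sociodemographic factors another role: "We will also explore the potential interaction effects between sociodemographic factors and mental health on neurodevelopment in CHD".

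**The concern.** If there are three latent constructs in all and one of them is prenatal factors, the model has a single mediator. A single mediator yields one indirect effect and therefore one proportion. The block-level proportions promised next are not parameters of that model and cannot be computed from its parameters.

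A single latent variable also treats its indicators as expressions of one common cause. The factors listed under Covariate measures (type of CHD, gestational age, maternal education, support, placental abnormalities) do not obviously share one.

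What is at stake is whether Aim 4 can say which prenatal factors carry the association. A model that pools them credits the mediated share to all of them together. If the conflict is left open until the data are in, the block structure may be chosen after results have been seen.

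**Working it through.** The article gives no figure for Aim 4, so there is nothing to reproduce. Its only sample size (72 dyads, 87 with attrition) belongs to the primary regression and does not bear on this point, except that 87 × 0.80 = 69.6, or about 70 dyads expected at follow-up.

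**Step 1: the model as written.** Let X be maternal mental health, M prenatal factors and Y child development. The paths are X→M (a), M→Y (b) and X→Y (c′).
- Indirect effect: a × b, one value.
- Proportion mediated: ab / (ab + c′), one value.

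**Step 2: the quantity promised.** With blocks k = 1, 2, 3 as parallel mediators, the proportion for block k is a_k·b_k / (Σ a_j·b_j + c′). This needs three a paths and three b paths. The written model has one of each.

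**Step 3: illustration at population level.** Assumed values, not from the article: each block is one standardised variable, a = 0.5 for every block, residual correlation between blocks 0.3, c′ = −0.2. A non-zero b of −0.4 gives a block effect of 0.5 × (−0.4) = −0.20. A one-latent-mediator model was fitted by maximum likelihood to the implied covariance matrix.

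| True block effects | One-latent indirect | Direct | Proportion |
|---|---|---|---|
| (−0.20, 0, 0) | −0.381 | −0.019 | 0.952 |
| (0, −0.20, 0) | −0.381 | −0.019 | 0.952 |
| (0, 0, −0.20) | −0.381 | −0.019 | 0.952 |
| (−0.20, +0.20, 0) | 0.000 | −0.200 | 0 |
| (−0.067, −0.067, −0.067) | −0.356 | −0.044 | 0.889 |

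In the first three rows the answer is identical whichever block mediates. In the fourth, two blocks mediate in opposite directions and the single effect is zero. A model with three parallel mediators returns the true block effects in every row. For row 1 it gives a proportion for block 1 of −0.20 / (−0.20 − 0.20) = 0.50.

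**Step 4: readings that might reconcile the text.**
- *A second-order prenatal-factors construct with the blocks beneath it.* There is still one structural mediator and one indirect effect.
- *A separate model for each block.* This conflicts with one model estimated simultaneously, and it would not apportion the effect among correlated blocks.
- *Three block mediators in one model.* This delivers the promise, but then the count of three latent constructs is wrong.

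**Step 5: neighbouring conflicts in the same paragraph.** The analysis text lists the CISS among the measures of maternal mental health, and so does the closing sentence of the Aim 4 objective. Yet that objective names coping strategies as mediators. Sociodemographic factors are interaction terms in the objective but sit inside the mediator in the analysis text.

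**The case against.** The best reply is that the article condenses a fuller document and that block-level mediators were probably intended. The sentence about three constructs has no main verb, which suggests abridged text. The reference to each block and the plural indirect effects both point to several mediators. The number three may be loose naming of three domains, and a full measurement model is detail that an article may leave out. Much of this stands: the text does not establish that a one-factor mediator will be fitted. It does not remove the conflict, because on the intended reading the sentence about three constructs still has to be changed.

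A second reply is that a badly fitting one-factor model would be noticed. With several indicators per block it often would be: in simulated scenarios at 70 dyads it failed the chi-square test at 5% in at least 95% of samples. That also depends on assumptions. In row 1 of the table the minimum discrepancy is 0.0694, so the noncentrality at 70 dyads is 69 × 0.0694 = 4.8 on 4 degrees of freedom, about 38% power. In the last row the discrepancy is zero and there is nothing to detect. Nor does a failed fit say which structure to use instead.

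A reader might also infer a definite loss of power or an inflated error rate. The documents do not support that. With only the psychological block mediating, simulated detection by a one-factor mediator at 70 dyads ran from 3% to 40%, depending on assumed loadings and between-block paths that the article does not give. It also states no block-level null hypothesis or test: it undertakes to explore and quantify, with confidence intervals.

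**Conclusion.** The point holds as an internal contradiction. Read literally, the Aim 4 model has one mediator, one indirect effect and one proportion, and it cannot supply the block-by-block proportions promised in the following paragraph. This rests only on the stated structure and on path algebra. The numbers in the table show what can happen under assumed paths and do not measure the harm in this study.

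The consequence is confined to a secondary aim with exploratory wording. The primary regression of the Bayley-4 cognitive score on the SCL-90-R, and its sample size, are untouched. The text should be corrected before outcome data are available, since as written it cannot answer the question that Aim 4 asks.

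**What to change.** In the Aim 4 analysis text, replace the single prenatal-factors latent variable with separate parallel mediators, one per block. Each may be a latent variable, a composite or a pre-named observed variable. Give each its own path from maternal mental health and its own path to child development, and let the mediator residuals correlate. Report every specific indirect effect with its bootstrap confidence interval and its proportion. If the single mediator is what is wanted, drop the per-block promise instead.

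Two points need settling in the same edit:
- If CISS coping scores act as mediators, as the objective implies, remove them from the maternal mental health construct so that coping does not sit on both sides of the same path.
- State whether sociodemographic factors are interaction terms or mediators, and use that role in both places.

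The cost is wording, plus a few more path coefficients to estimate at about 70 dyads. Observed mediators or composites would limit the number of added parameters.

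### The Aim 4 structural equation model puts sociodemographic and other pre-existing factors downstream of maternal distress, so any confounding by them would be reported as mediation; coping is also left with two roles

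*Protocol article*

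**What the plan says.** Under Data analysis plan, Aim 4, the Protocol article describes a structural equation model with three latent constructs. The exposure is "maternal mental health (as captured by SCL-90-R, STAI-Y, CISS, PCL-5 and EPDS scores"). The middle construct is "prenatal factors (medical, sociodemographic and psychological"). The outcome is child development on the Bayley-4 and ASQ-3. The ordering is one "whereby maternal mental health impacts prenatal factors, which in turn influence the" child's development, with a residual direct path from mental health to the outcome. The mediating role of each block is to be quantified by "estimating the proportion of the effect of maternal mental health on child development that is transmitted through those factors".

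Other sections give the same factors different roles:

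- **Aim 3, objective:** "To identify the medical and sociodemographic factors associated with prenatal maternal psychological distress of women carrying a fetus diagnosed with cyanotic CHD". Its hypothesis opens "We hypothesise that lower maternal educational attainment and poor family support as well as fetal factors such as diagnosis of severe CHD" and links these to worse maternal mental health.
- **Data analysis plan, Aims 2 and 3:** medical, sociodemographic and lifestyle variables are fixed effects, described as likely influences on the maternal questionnaire scores.
- **Aim 4, objective:** the mediators named are medical factors and coping strategies. Sociodemographic factors are to be explored through their interaction with mental health.
- **Data analysis plan, Main objective:** sociodemographic, medical and psychological factors are adjustment variables in the primary regression.

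Covariate measures lists type of CHD among the medical factors, and maternal education, marital status and support among the sociodemographic ones. Secondary outcome measures describes the CISS as measuring task-oriented, emotion-oriented and avoidance-oriented coping.

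**The concern.** An arrow from maternal distress to a factor claims that distress can change that factor. For variables settled before distress is measured, the claim is impossible. If such a variable also affects both distress and development, it is a common cause. Modelled as a mediator, it produces an indirect effect and a proportion mediated even when nothing is transmitted through it.

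The proportion mediated is the quantity that Aim 4 undertakes to report, block by block, and the Discussion wants the study to help target preventive strategies. A sociodemographic block reported as carrying part of the effect of distress would suggest a pathway that the data cannot show.

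The second difficulty is coping. Aim 4 names it as a mediator, and the CISS is the only coping scale described, yet the model lists the CISS as an indicator of the exposure. If the same scores inform both constructs, part of the exposure-mediator association arises by construction. If they inform only the exposure, the coping mediator has no stated measure among the questionnaires.

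**Working it through.** **1. Time order.** Mothers are assessed at T1, between 28 and 38 weeks of gestation and at least 4 weeks after the fetal diagnosis (Study design; Participants and recruitment). Type of CHD is established at diagnosis, before T1. Maternal education and marital status also normally precede T1. None of these can be an effect of T1 distress. Other listed medical items, such as fetal growth or hypertension in pregnancy, could follow distress.

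**2. Roles side by side.**

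| Factor | Aims 2 and 3 model | Aim 4 objective | Aim 4 model |
|---|---|---|---|
| Sociodemographic | influence on maternal scores | interaction with mental health | mediator block |
| Medical | influence on maternal scores | mediator | mediator block |
| Coping (CISS) | outcome score | mediator, and among the mental health scores | indicator of exposure; possibly also in the psychological block |

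The sociodemographic row has three different roles.

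**3. Size for one factor.** The plan gives no figure to reproduce here. Take standardised distress X, outcome Y and one observed pre-existing factor C.

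- r_xy = 0.45, in absolute value, from Sample size and power considerations.
- The shares of X and of Y explained by C are assumptions, because the article gives none. With equal shares s acting in the same direction, r_xc = r_yc = √s, so r_xc × r_yc = s.
- Direct coefficient = (r_xy − r_xc·r_yc) / (1 − r_xc²) = (0.45 − s) / (1 − s).
- Share labelled as mediated = (0.45 − direct) / 0.45.

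| Share of X and of Y | Direct coefficient | Labelled as indirect | Share labelled as mediated |
|---|---|---|---|
| 4% / 4% | 0.41/0.96 = 0.427 | 0.023 | 5% |
| 10% / 10% | 0.35/0.90 = 0.389 | 0.061 | 14% |
| 20% / 20% | 0.25/0.80 = 0.3125 | 0.1375 | 31% |
| 30% / 30% | 0.15/0.70 = 0.214 | 0.236 | 52% |

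If C is a cause of X, the share transmitted through C is zero in every row. The direct coefficient is the same under either ordering, because it is the coefficient of X adjusted for C. What changes is the remainder: the planned ordering calls it an indirect effect and adds it back into the total, whereas the reversed ordering calls it confounding.

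**4. Bootstrapping does not protect against this.** Simulated samples (1,000 per scenario, 400 resamples, percentile 95% intervals) had C causing both X and Y, and X affecting neither C nor Y. With assumed paths of 0.3 from C to each, the interval for the indirect effect excluded zero in about 50% of samples at n = 72 and 62% at n = 87. With assumed paths of 0.45 the figures were about 93% and 98%. The interval describes sampling error, not the direction of the arrow.

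**The case against.** Much can be said for the plan, and several stronger readings fail.

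- A reader might infer that the study's main conclusion is at risk. It is not. Aim 4 is secondary and worded as exploration, and the primary regression is separate and already adjusts for these categories.
- A reader might infer that every factor in the block is misplaced. The article does not say which medical items enter it. Covariate measures is a general inventory that includes growth, gestational diabetes, hypertension and placental abnormalities, which could follow distress. Type of CHD as a mediator is therefore an inference from the word medical; the sociodemographic category is explicit.
- A reader might take Aim 3 to assert causation. It speaks of association; directional language appears only in the Aims 2 and 3 analysis text.
- A reader might conclude that the effect-modification hypothesis, that some mothers "will experience the greatest effects of prenatal distress on their" children's outcomes, goes untested. The Aim 4 objective already commits to exploring interactions, and their specification may sit in a fuller document.
- A reader might conclude that the CISS is certainly entered twice. The model text lists it only under mental health. The Aim 4 objective gives the medical record, interview and information questionnaire as the sources for the mediating factors. This is an unresolved ambiguity.
- The direct path might be thought biased by the ordering. Step 3 shows that it is not.

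What stands is narrower: the stated arrow into an explicitly sociodemographic block, its conflict with two other parts of the article, and the unclear role of coping. The causal ordering is something the article states, so it cannot be excused as detail left to an analysis plan.

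**Conclusion.** The point holds in limited form. As written, Aim 4 treats pre-existing sociodemographic factors, and type of CHD if it is included, as consequences of third-trimester distress. To the extent that they affect both distress and development, the indirect effect and proportion mediated for those blocks are confounding. The spurious share runs from about 5% to 52% over assumed explained shares of 4% to 30%, for a single observed factor at a total correlation of 0.45. Latent blocks of several factors would give other values, and a factor unrelated to either variable would add nothing. The range shows sensitivity to assumptions and is not a forecast.

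The role of the CISS also has to be settled. This is a should-fix for a secondary, exploratory aim.

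**What to change.** In the Aim 4 model:

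1. Enter sociodemographic factors and type of CHD as exogenous variables, with paths into both maternal mental health and child development.
2. Limit the mediator blocks to factors that can follow T1 distress, for example fetal growth or gestational hypertension, and list them.
3. Take the CISS out of the mental-health measurement model, so that coping has the single mediator role that the Aim 4 objective states.
4. Examine the sociodemographic-by-mental-health interaction already announced as an exploratory Aim 4 analysis, outside the primary regression, so that the model behind the calculation of 72 dyads is unchanged.

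The cost is a revised paragraph and a little more modelling, with no new data. Fewer factors can then be reported as mediators.
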